# The REFANI-S study protocol: a non-randomised cluster controlled trial to assess the role of an unconditional cash transfer, a non-food item kit, and free piped water in reducing the risk of acute malnutrition among children aged 6–59 months living in camps for internally displaced persons in the Afgooye corridor, Somalia

**DOI:** 10.1186/s12889-017-4550-y

**Published:** 2017-07-06

**Keywords:** Acute malnutrition, Wasting, Cash transfer, Somalia, Study protocol, Internally displaced persons, Food security, Children

## Abstract

**Background:**

The prevalence of acute malnutrition is often high in emergency-affected populations and is associated with elevated mortality risk and long-term health consequences. Increasingly, cash transfer programmes (CTP) are used instead of direct food aid as a nutritional intervention, but there is sparse evidence on their nutritional impact. We aim to understand whether CTP reduces acute malnutrition and its known risk factors.

**Methods/design:**

A non-randomised, cluster-controlled trial will assess the impact of an unconditional cash transfer of US$84 per month for 5 months, a single non-food items kit, and free piped water on the risk of acute malnutrition in children, aged 6–59 months. The study will take place in camps for internally displaced persons (IDP) in peri-urban Mogadishu, Somalia.

A cluster will consist of one IDP camp and 10 camps will be allocated to receive the intervention based on vulnerability targeting criteria. The control camps will then be selected from the same geographical area. Needs assessment data indicates small differences in vulnerability between camps.

In each trial arm, 120 households will be randomly sampled and two detailed household surveys will be implemented at baseline and 3 months after the initiation of the cash transfer. The survey questionnaire will cover risk factors for malnutrition including household expenditure, assets, food security, diet diversity, coping strategies, morbidity, WASH, and access to health care. A community surveillance system will collect monthly mid-upper arm circumference measurements from all children aged 6–59 months in the study clusters to assess the incidence of acute malnutrition over the duration of the intervention. Process evaluation data will be compiled from routine quantitative programme data and primary qualitative data collected using key informant interviews and focus group discussions.

The UK Department for International Development will provide funding for this study. The European Civil Protection and Humanitarian Aid Operations will fund the intervention. Concern Worldwide will implement the intervention as part of their humanitarian programming.

**Discussion:**

This non-randomised cluster controlled trial will provide needed evidence on the role of unconditional CTP in reducing the risk of acute malnutrition among IDP in this context.

**Trial registration:**

ISRCTN29521514. Registered 19 January 2016.

## Background

Acute malnutrition in childhood is a serious global health concern affecting an estimated 50 million children aged <5 years in low- and middle-income countries [1, 2]. Acute malnutrition is a leading cause of childhood mortality, accounting for 11.5% of total deaths, and contributes significantly to the overall disease burden [3]. The prevalence and severity of acute malnutrition is usually greater in populations affected by emergencies- such as in natural disasters or conflicts [4].

Because of a prolonged state of instability and conflict, coupled with natural disasters, Somalia has one of the highest global prevalences of child acute malnutrition [5]; with the south-central region consistently exceeding the critical prevalence threshold of 15% (Fig. 1) [6]. The state of conflict has disrupted not only regional agriculture and trade, but also humanitarian access, forcing displacement and increasing mortality [7]. Furthermore, trade disruption has exacerbated food insecurity due to increased food prices, especially in urban areas [7]. An estimated 304,700 children aged <5 years were acutely malnourished in Somalia in early 2016, of which 58,300 were severely malnourished [6]. The group most affected by food insecurity and acute malnutrition are internally displaced persons (IDP), who often live in camps.

**Fig. 1 Fig1:**
[figure not shown]
Trends in Global Acute Malnutrition (GAM) in the south-central region of Somalia. Adapted from reference [6]

There are various nutritional interventions commonly used for the management of acute malnutrition [8]. Among these, cash transfer programmes (CTP) have recently gained popularity compared to conventional food-based interventions [9]. CTP may involve a conditional or unconditional cash or voucher transfer to beneficiaries, with the aim of improving their ability to acquire food and/or other needs. While food security and nutrition are objectives often stated for CTP, they frequently have multi-sectoral objectives and may also be intended to enable livelihood investments [10, 11]. Furthermore, CTP are perceived to reduce the cost of nutritional and related interventions, improve beneficiary satisfaction, and have a positive impact on local economies [11]. CTP were first implemented at scale in Somalia in 2011 to respond to the famine crisis. CTP were made possible by the existence of functioning markets and were seen as an essential approach given the lack of humanitarian access to parts of South Central region that made the provision of food aid impossible [12]. Nonetheless, the suitability and nutritional impact of CTP needs further evaluation in order to measure their impact on acute malnutrition in emergencies and understand the mechanisms through which they may act.

## Methods/design

### Objectives

To conduct a non-randomised cluster-controlled trial to assess the impact of an unconditional CTP on acute malnutrition and its associated risk factors in children aged 6–59 months, living in IDP camps in the Afgooye Corridor, a region close to Mogadishu, Somalia.

### Hypotheses

We have two hypotheses. 1. Unconditional cash transfers reduce the risk of developing acute malnutrition in children aged 6–59 months. 2. Unconditional cash transfers reduce known risk factors for acute malnutrition in IDP camps located in a peri-urban area of Mogadishu, Somalia.

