### Study setting and population

The study will be conducted in IDP camps located in Weydow area, Deyniile district, Mogadishu. Deyniile and Dharkenley, two of the 17 districts of Banaadir region, host the majority of IDP in Mogadishu, who are primarily from marginalised tribes or minority groups [13]. Concern Worldwide (hereafter Concern) has been implementing multi-sector development and humanitarian assistance programmes in this setting.

The IDP camps in Weydow area are privately run, spontaneous settlements that are often overcrowded, lack basic sanitation and health services, and face recurrent evictions. Morbidity (diarrhoea, pneumonia, and fever) estimates in these camps are high and may be a major driver for high global acute malnutrition (GAM) estimates [6]. During the wet seasons (Gu and Deyr, Apr-Jun and Oct-Dec, respectively), morbidity estimates are particularly high, mainly due to diarrhoea [6].

Most of the IDP were previously agro-pastoralists and riverine farmers that lived in the Bay, Bakool, and Shabelle regions [13]. Currently, their primary livelihoods sources are casual labour, petty trading, and humanitarian assistance received from local and international humanitarian organisations [6].

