### Intervention

The intervention will comprise a monthly unconditional CTP of US$ 84.00/month for 5 months, a once-only distribution of a non-food items (NFI) kit, and the provision of piped water through tap stands.

The monthly cash amount was based on the cost of the Minimum Expenditure Basket (MEB) developed by the FAO’s Food security and Nutrition Analysis Unit (FSNAU). The MEB represents a minimum set of basic food items such as sorghum, vegetable oil and sugar, comprising 2100 kcal/person/day basic energy requirement for a household of 6–7 members, and non-food items such as such as water, kerosene, firewood, soap and cereal grinding costs. As a reference, Fig. 2 shows the historical cost of MEB in the Banaadir region from January 2011 to December 2016.

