## Discussion

This study began in March 2016 but due to field-based challenges, some modifications from the study protocol have occurred. Initiation of the unconditional CTP was delayed from March to May. Early preliminary data analysis of the surveillance system data also suggested that there was excess under-5 mortality in the study population and this prompted us to include Verbal Autopsy interviews, a method that will enable identification of the probable causes of death [24, 25].

Formative work has been undertaken and further qualitative work will be undertaken by the same team that did the quantitative data collection instead of a separate team as originally planned, because of the challenges of recruiting technical personnel with qualitative data collection experience that are willing to work in the field sites in Somalia. The staff involved have limited experience of qualitative data collection so additional training will be supplied before they start data collection. The study design presented here will provide the first robust evidence of the impact of cash transfers on the incidence of malnutrition in an emergency context with high levels of insecurity.

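### The question and claims name unconditional cash, but the two arms differ by cash, a non-food items kit and piped water together, so the effect of cash cannot be isolated

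*Protocol article*

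**What the plan says.** All references are to the protocol article.

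**What is delivered.** The title, the abstract's Methods/design and the Intervention section agree on three components. Besides the monthly cash there is "a once-only distribution of a non-food items (NFI) kit, and the provision of piped water through tap stands". The kit includes soap, mosquito nets and jerry cans.

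**Who gets it.** Under Study design, all households in the 10 selected camps are registered for the intervention. The control arm is 10 adjacent camps that do not get it. Outpatient therapeutic and maternal and child health care is given as an example of services available to both arms.

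**What is asked.** The Objectives are "to assess the impact of an unconditional CTP on acute malnutrition and its associated risk factors in children aged 6–59 months". Hypothesis 1 begins "Unconditional cash transfers reduce the risk of developing acute malnutrition in children" and hypothesis 2 begins "Unconditional cash transfers reduce known risk factors for acute malnutrition in IDP camps". The aim in the abstract's Background likewise concerns cash transfer programmes only.

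**What is promised.** The Discussion says the design "will provide the first robust evidence of the impact of cash transfers on the incidence of malnutrition". The abstract's Discussion also refers to unconditional cash alone among the components.

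**How it is analysed.** Under Data analyses, the survey outcomes are compared by difference-in-differences between arms, and incidence by a Cox model across the trial arms.

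**The concern.** The exposure in the question differs from the exposure that separates the arms. Each intervention camp is assigned all three components and each control camp is assigned none of them as part of the trial. Within the comparison, cash therefore never varies separately from the kit and the water. A difference between arms could come from any of the three or from a combination, yet the objective, hypotheses and Discussion would credit it to cash.

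The Background motivates the study by the need to evaluate cash transfers themselves as a nutritional intervention. Readers choosing between cash and other aid are those most likely to take a package effect as a cash effect.

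**Working it through.** **1. What the planned incidence comparison is powered for.** Inputs from Sample size calculation: hazard ratio 0.5, power 80%, alpha 0.05 (taken as two-sided; the article does not say), 7% developing acute malnutrition over 6 months, 20% loss to follow-up. Equal arms are assumed.

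- Events (Schoenfeld) = 4 × (1.960 + 0.842)² / (ln 0.5)² = 65.35.
- Children = 65.35 / 0.07 / (1 − 0.20) = 1167.

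This reproduces the stated total of 1167. The calculation contains one contrast, arm against arm, and no term for a component. Full power would still yield only the hazard ratio for cash, kit and water combined.

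**2. Whether any planned analysis separates the components.** Let C, K and W mark assignment to cash, kit and water. Intervention camps have C = K = W = 1 and control camps have C = K = W = 0, so the three indicators are identical across all 20 camps. A Cox model or a difference-in-differences model can estimate one coefficient for them, not three. A separate analysis plan could not change this, because the limit is in the allocation. The Discussion reports that the start of the cash slipped from March to May but does not mention the kit or the water. The documents therefore offer no basis for separating components by start date.

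**3. What a package result would say about cash.** Purely as an illustration, assume effects multiply, so that package HR = cash HR × non-cash HR. For a package HR of 0.5:

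| Assumed non-cash HR | Implied cash HR |
|---|---|
| 1.0 | 0.5 / 1.0 = 0.50 |
| 0.8 | 0.5 / 0.8 = 0.625 |
| 0.5 | 0.5 / 0.5 = 1.00 |

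Every row fits the same trial result equally well. The documents give no value for the non-cash HR, so none of the rows is an estimate.

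**4. Whether the non-cash components have a plausible route to the outcomes.**

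- *Hypothesis 1.* Study setting and population names morbidity (diarrhoea, pneumonia and fever) as a possible major driver of acute malnutrition. It adds that in the wet seasons "morbidity estimates are particularly high, mainly due to diarrhoea". Water, soap, jerry cans and nets could act on morbidity. The planned intervention months in Table 1, March to July, cover the April to June wet season.
- *Hypothesis 2.* The Intervention section bases the cash amount on a basket that includes water and soap. Free water supplies in kind something the basket prices. It could free money for food and so shift expenditure and dietary diversity, the latter a primary outcome.

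**The case against.** The strongest reply is that this is loose labelling. The title, the abstract's Methods/design and the Intervention section disclose the package, and the analysis compares the arms as they are. Nowhere does the article say that cash will be assessed independently of the other components. That stands as far as disclosure goes: nothing is concealed, and the planned contrast already is package against no package. It does not remove the mismatch, because the hypotheses and the Discussion claim still name an exposure that the contrast does not isolate.

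Other parts of the reply limit the point:

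- A reader might infer that control households have no piped water or comparable goods. The article says only that control camps do not receive the intervention. It does not describe their existing water supply, or whether residents of these adjacent camps can use the tap stands. The real difference in water access may be small.
- A reader might infer that the article blames diarrhoea for acute malnutrition. It names morbidity in general as the possible driver and ties the predominance of diarrhoea to the wet seasons only.
- The two hypotheses are not equally exposed. Cash of US$84 × 5 = US$420 per household bears directly on diet and expenditure, whereas water and the kit reach those outcomes indirectly.
- WASH, morbidity, asset and expenditure data are already collected in both arms, and the process evaluation already explores mechanisms. Neither can separate the components' effects, but no new data collection is called for.

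**Conclusion.** The point holds as a mismatch between the intervention delivered and the effect claimed. The plan promises evidence on cash transfers, while its design can deliver evidence only on the package. This follows from the allocation and needs no assumption about effect sizes.

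Its size cannot be stated. The share of any effect due to the kit and water is unknown, and the hazard ratios in the table are assumed values showing only that the data could not discriminate between them. A reader might go further and conclude that a positive result would be due to water rather than cash, or that the trial is uninformative. The documents support neither. Cash may account for all of the effect, and the package comparison is a legitimate question. Whether non-randomised allocation biases that comparison is a separate matter.

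**What to change.** Restate the aim (abstract Background), the Objectives, both Hypotheses and the claims in the abstract's Discussion and the main Discussion as the effect of the combined package (cash, non-food items kit and piped water) against no package, in line with the title. Add one sentence saying that the effect of cash itself cannot be isolated in this design.

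Label the WASH, morbidity and expenditure comparisons by arm as exploratory pathway evidence. They can show whether a pathway moved, not which component moved it. Carry the same wording into the reports of results.

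The cost is a narrower claim. The sample size of 1167, the Cox model and the difference-in-differences analysis stay as they are, and no new data are needed.

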### Study setting and population

The study will be conducted in IDP camps located in Weydow area, Deyniile district, Mogadishu. Deyniile and Dharkenley, two of the 17 districts of Banaadir region, host the majority of IDP in Mogadishu, who are primarily from marginalised tribes or minority groups [13]. Concern Worldwide (hereafter Concern) has been implementing multi-sector development and humanitarian assistance programmes in this setting.

The IDP camps in Weydow area are privately run, spontaneous settlements that are often overcrowded, lack basic sanitation and health services, and face recurrent evictions. Morbidity (diarrhoea, pneumonia, and fever) estimates in these camps are high and may be a major driver for high global acute malnutrition (GAM) estimates [6]. During the wet seasons (Gu and Deyr, Apr-Jun and Oct-Dec, respectively), morbidity estimates are particularly high, mainly due to diarrhoea [6].

Most of the IDP were previously agro-pastoralists and riverine farmers that lived in the Bay, Bakool, and Shabelle regions [13]. Currently, their primary livelihoods sources are casual labour, petty trading, and humanitarian assistance received from local and international humanitarian organisations [6].

### Intervention

The intervention will comprise a monthly unconditional CTP of US$ 84.00/month for 5 months, a once-only distribution of a non-food items (NFI) kit, and the provision of piped water through tap stands.

The monthly cash amount was based on the cost of the Minimum Expenditure Basket (MEB) developed by the FAO’s Food security and Nutrition Analysis Unit (FSNAU). The MEB represents a minimum set of basic food items such as sorghum, vegetable oil and sugar, comprising 2100 kcal/person/day basic energy requirement for a household of 6–7 members, and non-food items such as such as water, kerosene, firewood, soap and cereal grinding costs. As a reference, Fig. 2 shows the historical cost of MEB in the Banaadir region from January 2011 to December 2016.

**Fig. 2 Fig2:**
[figure not shown]
The cost of a Minimum Expenditure Basket (MEB) in the Banaadir region, 2011–2016. Data obtained and adapted from the FSNAU website (http://www.fsnau.org/sectors/markets). The MEB cost is calculated based on a minimum set of basic food items such as sorghum, vegetable oil and sugar, that will supply 2100 kcal/person/day for a household of 6–7 members, and non-food items such as such as water, kerosene, firewood, soap, and cereal milling costs

Upon registration, a household female representative will receive a mobile phone SIM card with a unique number, through which they will receive the transfer via a mobile money transfer company. The intervention will target women as the household cash recipient, on the assumption that their spending is more likely to benefit their children [14].

The NFI kit will comprise one plastic sheet, two mosquito nets, one blanket, one sleeping mat, one kitchen set, one bar of soap, two collapsible jerry cans, and one set of sanitary pads.

Concern will also continue to provide support and equipment to the local Maternal and Child Health and Nutrition (MCHN) centres and Outpatient Therapeutic Programmes (OTP), where malnourished children and pregnant and lactating mothers of the study area will be referred for treatment. Improved pit latrines have been provided by Concern and other NGOs in most of the camps included in the study.

### Study design

The study design is a non-randomised cluster controlled trial. Concern will implement a routine needs assessment exercise to identify vulnerable beneficiaries and on that basis select the camps that will receive the intervention. All households in the selected camps will be registered for the intervention. A non-randomised design was chosen as the best available approach in this setting because the intervention will be allocated based on vulnerability criteria.

The cluster unit in the trial will be an IDP camp and the intervention arm will include 10 IDP camps selected to receive the intervention. The reason that only 10 camps can be selected to receive the intervention is the limit in the donor funding that is available to provide services in this area. The control arm will include another 10 IDP camps, located adjacent to the intervention camps that will not receive the intervention. Routine programme data suggests small differences in vulnerability between camps. Households in both arms will benefit from the services provided by Concern, such as care from OTP and MCHN centres.

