### Study components

Data collection will consist of three main components:
*Household surveys of malnutrition risk factors*. To evaluate the impact of the intervention on known malnutrition risk factors two detailed household surveys will be implemented, the baseline survey will be undertaken before the intervention begins and the endline one 3–4 months after the start of the intervention.Based on our working assumption that insecurity in the field will constrain the possibility of following-up the baseline sample, the surveys will select independent samples of households from the study clusters at the two periods. If security conditions are worse than anticipated and do not allow sampling within a sufficient number of clusters, then we will collect data from a single control and intervention cluster and the data will be analysed as a before and after comparative cross-sectional study. Furthermore, if security conditions do not allow us to undertake repeated surveys in the same clusters, then we will undertake a single survey at the end of the intervention, and the data will be analysed as a cross-sectional study. However, if field conditions are better than anticipated, we will follow-up the baseline sample and the data will be analysed as a longitudinal cohort.The surveys will collect data at the household level and from all the children aged <5 years and their mothers/carers living in the selected households. The data collected in these surveys will comprise data on household demographics, household expenditure and income, assets, food security, diet diversity, coping strategies, morbidity, WASH, access to health care, and infant and young child feeding practices. The surveys will also collect anthropometric data from children to describe their nutritional status. However, this anthropometric data will not be used to assess the impact of the intervention due to sample size limitations (see below).
*A community surveillance system* will be set up to collect anthropometric data that will be used to evaluate whether the intervention reduces the risk of developing acute malnutrition. In this surveillance system, community health workers (CHW) will collect monthly mid-upper arm circumference (MUAC) measurements to detect the incidence of acute malnutrition in an exhaustive sample of children aged 6–59 months from both intervention and control clusters. Those identified as malnourished will be referred to nutrition centres for treatment.

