### Data analyses

Data analysis will be undertaken using Stata. Prevalence estimates at baseline and endline, will be computed using the *svy* commands which allows for the clustering of values. We will test for endline minus baseline difference-in-differences between the study arms using the data collected in the malnutrition risk factor surveys. Analysis of the incidence of acute malnutrition in the trial arms will be performed using Cox Proportional Hazards analysis. All results will be reported according to STROBE recommendations for observational studies [21].

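### Camps are selected on vulnerability, but the Cox analysis stated for the primary incidence outcome names no baseline correction, while the survey outcomes get one

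*Protocol article*

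**What the plan says.** On allocation (protocol article, Study design): "Concern will implement a routine needs assessment exercise to identify vulnerable beneficiaries and on that basis select the camps that will receive the intervention". This is given as the reason for not randomising: "A non-randomised design was chosen as the best available approach in this setting because the intervention will be allocated based on vulnerability criteria". On the controls: "The control arm will include another 10 IDP camps, located adjacent to the intervention camps that will not receive the intervention". No matching of camps is described.

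On the size of the imbalance, the article offers a qualitative statement in two places. The Abstract says "Needs assessment data indicates small differences in vulnerability between camps" and the Study design section says "Routine programme data suggests small differences in vulnerability between camps". Neither gives a figure.

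On analysis (Data analyses), the survey outcomes, which include the second primary outcome (individual diet diversity score), are handled as follows: "We will test for endline minus baseline difference-in-differences between the study arms using the data collected in the malnutrition risk factor surveys". For the first primary outcome the whole statement is: "Analysis of the incidence of acute malnutrition in the trial arms will be performed using Cox Proportional Hazards analysis". It names no covariate, weighting, matching or pre-period contrast. It also does not call the model unadjusted.

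On available data (Study components), community health workers "will collect monthly mid-upper arm circumference (MUAC) measurements to detect the incidence of acute malnutrition" among all children aged 6–59 months in both arms. Under Data collection the text starts surveillance in March 2016, while Table 1 already marks February. The Discussion reports that the cash transfer was put back from March to May.

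**The concern.** The variable that decides which camps are treated is one that would be expected to predict a MUAC below 12.5 cm. If the more vulnerable camps are treated, their underlying hazard is probably higher, and an arm comparison without baseline correction would hide some of a real benefit or suggest harm. Regression to the mean after selection at a bad moment could push the other way and imitate benefit.

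The two primary outcomes are treated differently within one paragraph. The diet score gets a contrast that cancels fixed differences in level, and incidence gets a contrast that does not. Yet incidence is the outcome that tests the first hypothesis, and monthly MUAC from both arms before cash began should be available to correct it.

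**Working it through.** **Step 1. Reproduce the plan's sample size.** Inputs from Sample size calculation: hazard ratio 0.5, 7% developing acute malnutrition in 6 months, 20% loss, power 80%, alpha 0.05. Sidedness is not stated; two-sided with equal arms reproduces the figure.

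- Events (Schoenfeld) = (1.960 + 0.842)² / (0.25 × ln(0.5)²) = 65.35
- Children = 65.35 / 0.07 / 0.80 = 1166.9, so 1167, as stated

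This calculation takes the arms to have the same hazard apart from the intervention.

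**Step 2. Add a pre-existing difference.** Let *b* be the intervention-to-control hazard ratio that would exist without the intervention. The documents give no value, so the range is an assumption. With proportional hazards, a constant *b* and no adjustment:

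- expected hazard ratio = *b* × true hazard ratio
- probability of significant benefit = Φ(−ln(expected HR) × √(E/4) − 1.960), with E = 65.35 and clustering ignored

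| Assumed *b* | Expected HR if true HR is 0.5 | Power for benefit | Two-sided rejection if true HR is 1 |
|---|---|---|---|
| 0.8 | 0.40 | 96% | 14.7% (14.5% false benefit) |
| 1.0 | 0.50 | 80% | 5.0% |
| 1.1 | 0.55 | 68% | 6.7% |
| 1.2 | 0.60 | 54% | 11.4% (11.1% false harm) |
| 1.3 | 0.65 | 41% | 18.5% (18.4% false harm) |

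Worked line for *b* = 1.2: 1.2 × 0.5 = 0.60; 0.511 × √(65.35/4) = 2.065; Φ(2.065 − 1.960) = 0.54. Events for 80% power at 0.60 would be 4 × 7.849 / ln(0.6)² = 120.

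**Step 3. Does a larger sample help?** The article expects more children than planned. The expected hazard ratio in Step 2 does not depend on E, so the bias stays. More events only make the test surer of the wrong value. With four times the events (261.4), *b* = 1.2 and no true effect, ln(1.2) × √(261.4/4) = 1.474, and false harm is 1 − Φ(1.960 − 1.474) = 31%, against 11.1% at the planned size.

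**Step 4. How much can the pre-cash months tell us on their own?** Take 1200 children, a constant hazard and two months (March and April): 1200 × 0.07 × 2/6 = 28 events. The standard error of the log hazard ratio is about 2/√28 = 0.38, so a 95% interval around 1.0 runs from about 0.48 to 2.1 before clustering. That cannot detect a ratio of 1.1 to 1.3. A pre-period contrast of incidence is therefore a weak check at the planned size.

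**The case against.** The strongest reply is that the article never says the model is unadjusted. Cox regression carries covariates, and a condensed article may leave the covariate list to a fuller document. A reader might infer from the single sentence that a raw arm comparison has been fixed. The text does not support that; it supports only that no correction is named. What remains is more than a missing list: control of confounding is central to a design that allocates on vulnerability, and the same paragraph names a baseline-corrected contrast for the other primary outcome.

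The article also limits the problem in ways that count. Control camps are adjacent and from the same area, both arms use the same treatment and maternal and child health services, outside relief and security events are recorded, and results are to be reported as for an observational study. These features make a large imbalance less likely. They do not correct for one.

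A reader might go further and infer that the primary hazard ratio cannot be interpreted, or that power will fall to about 54%. Neither is shown. The 1.1 to 1.3 range is assumed, against documents that speak only of small differences, and the direction of bias is not known. Planned events are also a floor, since enrolment is exhaustive and surveillance is to last about a year rather than the 6 months used for sizing. The power figures are therefore tied to a size the article expects to exceed, but the bias is not.

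Finally, it is tempting to say that everything needed for correction is already collected. That is too strong:

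- No numeric camp vulnerability score is described.
- The article does not say that the surveillance form records age and sex.
- The detailed risk-factor data come from 120 sampled households per arm, with no described link to the surveillance children.
- Only the cash start is reported as delayed. The actual start dates of the non-food item kit and piped water are not given, so March and April MUAC may not precede every component.

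**Conclusion.** The point holds in a limited form. Allocation depends on a likely predictor of the outcome, and the only analysis stated for primary incidence is an arm comparison with no baseline correction named. Run as stated, it carries any pre-existing difference in risk into the hazard ratio one for one on the multiplicative scale: 0.5 becomes 0.55 to 0.65 for an assumed ratio of 1.1 to 1.3, or 0.40 for an assumed 0.8. This rests on proportional hazards, a constant pre-existing ratio and the absence of adjustment. The documents do not establish that the model will be unadjusted, that the imbalance is of this size, or which way it runs. The point is worth settling because a better method is within reach at the cost of analysis wording.

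**What to change.** In Data analyses, state that the primary Cox model for incidence is adjusted for pre-intervention MUAC from the surveillance system:

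- **Child level:** the last MUAC before any intervention component (cash, kit or water) began, where available. Give the actual start date of each component so that this value is a true baseline, and count time at risk in the primary model from then.
- **Camp level:** the camp's pre-intervention mean MUAC, or its pre-intervention prevalence of MUAC below 12.5 cm. This applies to all children, including those who enter later and have no pre-intervention value of their own.
- **Age and sex**, if the surveillance form records them.

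Report the unadjusted hazard ratio alongside, and put a figure on the difference in vulnerability that is now only described as small.

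Keep two further analyses as sensitivity analyses only. One adds the camp needs-assessment measure, if it exists in numeric form; because camps were selected on it, it may be collinear with arm. The other is an arm-by-period (before/during) Cox model, which rests on about 28 pre-period events at the planned size.

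The cost is modest analysis work and one camp-level degree of freedom among 20 camps. No new fieldwork is needed for the MUAC terms, provided surveillance began before every component. Adjustment reduces confounding but cannot guarantee its removal, and the report should say so.
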